## JUSTIFICATION OF METHODOLOGICAL CHOICES

Critics of non-drug interventions and FR claim that the effect is only placebo or related to management and patient/therapist interaction. This is why, in the present study, we propose to study the impact of FR management compared to a sham massage (SM), with the same reflexologist practitioner, in order to avoid a bias related to the personality of the therapist and therefore to the patient's care.

In addition, the patient will be informed that he or she will be randomly selected to benefit from an analgesic NPI, explaining that two different techniques are being studied in this protocol. The patient will thus be blinded.

In order to ensure objective evaluation and blinded data analysis, the person in charge of pain assessment of Parkinson's patients will not be informed of the patient's randomization. This is why we talk about double-blind in this study.

The rigorous evaluation of pain in this study led us to select many questionnaires that evaluate the different aspects of pain. This will allow us to cross-reference the different information in order to strengthen the observation of the impact of the management of FR.

## BENEFIT/RISK RATIO

Participants in the experimental group of the DOREPAR study will have a direct individual benefit in the short term since we postulate that the treatment will allow an improvement in chronic pain in patients with PD. Patients in the control group (SM) will benefit from close care and follow-up that includes massages.

In the long term, the benefit should be collective because it will make it possible to better manage pain, which can be particularly disabling for Parkinson's patients with an expansion of the care offer.

There is no risk associated with this research.

We therefore consider this research to have a favourable benefit/risk ratio.

## EXPECTED BENEFITS

This study proposes an **innovative approach** to the management of chronic pain for Parkinson's patients in this study by RP.

▪ **Expected outcomes directly for patients in the study**

Through this project, we propose a FR protocol whose content has been standardized, exploring the effectiveness of this management through different markers and scales, compared to an SM. This study will thus make it possible to better specify the uses and represents an essential step in validating the impact of FR on patients' chronic pain in a comparative approach. Based on experience and observation, we postulate that this management (of 4 FR sessions) should lead to clinically relevant improvement in chronic pain.

- **Preliminary data: solid basis for a larger study**

All the elements collected will constitute preliminary data that will allow us to subsequently design a larger research project. These data will make it possible to validate their effectiveness in terms of benefits for patients (reduction of chronic pain, quality of life, stress management), as well as to propose brain imaging biomarkers of potential brain changes that occur during pain reduction in PD patients.

- **Expected long-term impact on the Parkinson's patient population** In the population of Parkinson's patients with chronic pain, the use of FR could be beneficial in terms of:
- **by improving the perception of pain and therefore the daily life of patients,**
- **by avoiding the use of pharmacological analgesics and their possible side effects.**

In the long term, the challenge is to provide new tools in the management of chronic pain, to have reliable information to better inform patients and to enable health professionals to recommend RP as a complementary therapeutic method in an informed manner.

## RATIONALE FOR LOW LEVEL OF INTERVENTION

This project involves a low level of intervention since foot reflexology is a very well tolerated and non-invasive method.

The patient will have to come every 3 weeks for 3 months to benefit from either FR or SM.

Brain fMRI examination without contrast agent injection at the beginning and end of the study also presents a minimal risk.

We therefore consider that it falls within the framework of interventional research with minimal risks and constraints (category 2 of the Jardé law).

**3. RESEARCH OBJECTIVES**

## MAIN OBJECTIVE

The main objective is to evaluate the variation in the mean intensity of chronic pain by FR measured by a Visual Analogue Scale (VAS) over the last 7 days in PD patients after 4 sessions of FR at a rate of one hour session every 3 weeks compared to a group of patients receiving 4 sessions of a sham massage (SM) of the same duration and frequency.

## SECONDARY OBJECTIVES

The secondary objectives are:

1. To compare the number of patients with at least 30% improvement in pain on VAS after management between the 2 groups of patients (FR vs SM).
2. To compare the kinetic variation in the analgesic effect of a 4-session PR treatment on the intensity of chronic pain measured by a Visual Analogue Scale (VAS) during management between the 2 groups of patients (FR vs SM).
3. Comparing the variation in chronic pain using King's Parkinson's disease Pain

Scale (KPPS) and the Brief Pain Inventory (BPI), and the Primary Parkinsonian Pain Diagnostic Questionnaire (3PDQ) before and after the overall management between the 2 groups of patients (PR vs. MS).

1. Compare the evolution of the subjective nociceptive threshold and the tolerance to heat using the thermotest between the 2 groups of patients (FR vs SM):

a) before and after overall support between V1 and V4

1. Compare analgesic consumption using a diary of analgesic treatments throughout the study, before and after treatment between the 2 groups of patients (FR vs SM).
2. To compare pain acceptance with CPAQ-8, anxiety and depression with HAD, before and after management between the 2 groups of patients (PR vs. MS).
3. To determine if there are biomarkers of the effect of RP on brain activity using fMRI before and after management between the 2 groups of patients (RP vs MS).
4. To assess whether there are personality traits that modulate the analgesic response in the 2 groups of patients (according to the results obtained in the TCI personality test)

**4. JUDGING CRITERIA**

### 4. PRIMARY OUTCOME

The primary outcome of this study is the variation in mean pain intensity during the previous week, rated on an VAS (from 0 = no pain to 10 = maximum imaginable pain), before and after management between the 2 groups of patients (FR vs SM). Pain intensity on VAS is a validated clinical criterion for the global assessment of the discriminative and emotional aspects of pain *[Price 1994].*

We chose to assess the intensity of the overall pain and not the intensity of the different types of pain. Indeed, we believe that this type of intervention can have a non-specific effect on pain and therefore reduce the perception of pain in general and thus improve the daily life of patients. The variation corresponds to the raw delta between the VAS score at baseline (V1) and that after the 4 sessions of FR vs SM at the last visit (V5).

## SECONDARY OUTCOMES

The impact of the management in the 2 groups of patients (FR vs SM) will also be evaluated through:

1. The number of responding patients, i.e. who have at least a 30% improvement in their pain on VAS after overall management.
2. The kinetics of the pain intensity curve (assessed with the VAS over the last 7 days) between baseline and each visit. There are therefore 4 mean deltas for each group of patients *[Price 1994].*
3. At the deltas of the following scores, before and after global management:
   - of the KPPS *[Chaudhuri 2015]* which is a reliable and validated scale in the assessment of pain intensity in Parkinson's disease. It includes 14 questions grouped into 7 areas.

Each item is rated according to severity (between 0 and 3) and multiplied by frequency (between 0 and 4). A subscore between 0 and 12 is obtained for each item. The total score is between 0 and

168 by adding up all the sub-scores.

- - of the BPI *[Brasseur 1997]* which evaluates different dimensions of pain such as functional disability, as well as social and psychological impacts. It includes 7 items that patients rate between 0 (no discomfort) and 10 (maximum discomfort).
  - of Mac Gill *[Turk 1985]* which is a self-questionnaire that describes the type of pain and quantifies its intensity. It evaluates the sensory-discriminative dimension and the affective dimension of pain separately. There are 15 items, 8 of which are for the sensory-discriminative dimension and 7 for the affective dimension. Each item is rated between 0 (absent) and 4 (strong).
  - 3PDQ, which is a self-questionnaire currently being validated in France that would make it possible to diagnose primary Parkinson's pain. It includes 20 closed-ended questions.

1. At the threshold of subjective pain perception to heat and tolerance to heat. For each patient in ON condition (i.e. when the patient has taken his or her anti-Parkinson's treatment in the usual way) we will determine their variations:
   - - before/after the session at visit 1,
     - before/after the session at visit 4,
     - between V1 and V4 before the session is carried out,
     - between V1 and V4 after the session has been carried out, - .
     - For the threshold of subjective pain perception in warmth, thermal stimulations will be performed using a thermotest (MSA Thermotest, Somedic AB, Sweden) *[Frushstorfer 1976].* A 12x25mm contact thermode will be placed in contact with the patient's thenar eminence. We will determine the nociceptive threshold specific to each subject. To do this, we will use the threshold method which does not depend on the reaction time *[Gescheider 1985; Gracely 1987].* The determination of the pain threshold will be carried out on the hemibody most affected by the disease; This will be determined by the interview (the patient's feelings, laterality of the symptoms at the beginning of the disease) and confirmed by the clinical examination (part III of the UPDRS: rigidity, tremor and akinesia).

*Method of levels* : The initial temperature of the thermode being 30ºC, the patient will receive a temperature of +3°C for 30 seconds. Immediately after each thermal stimulation, the patient will be asked whether or not they have felt a painful sensation (yes/no); If the answer is no, the temperature will then be increased by 3ºC and applied again for 30 seconds, until the patient feels a painful sensation; In case of a positive response, the temperature will be lowered by 1.5°C (half of 3°C) and applied again for 30 seconds. The threshold will then be gradually adjusted until a temperature between two intervals close to 0.2ºC is obtained. An interval of 30 seconds was respected between each stimulation. Two sets of stimulations will be performed and the subjective threshold will be defined as the average of the two.

- - - For the tolerance to heat, starting from the subjective threshold determined above, we will determine: the Intensity-Response curve

After determining the nociceptive thresholds for heat, a series of supraliminal hot thermal stimuli will be randomly applied. Each stimulus will last 5 seconds and have a maximum intensity of 48°C and a minimum of 5°C. An interval of 60 seconds will be respected between each stimulation.

After each stimulus, the patient will be asked to rate the pain felt using a Visual Scale

Analogue (VAS from 0=no pain to 10=unbearable pain). This will allow us to establish a response intensity curve (EVA) as a function of temperature. Tolerance to heat

From the Intensity-Response curve, we will be able to determine the temperature for which the VAS was equal to 75%. This temperature will then be applied twice at five-minute intervals to the patient, who will have to orally express his tolerance threshold (which corresponds to the time before the stimulation becomes unbearable).

1. Consumption of analgesics by means of a collection booklet throughout the study (collection of the prescribed treatment and dosage).
2. At the deltas of the following scores, before and after global management:
   - CPAQ-8 pain acceptance test *[McCracken 2004]*. This self-questionnaire assesses the acceptance of chronic pain via 8 statements. Each item is rated between 0 (never true) and 6 (always true).
   - of the HAD scale *[Lépine 1985]*. It is a self-questionnaire to screen for anxiety/depressive disorders. Patients answer 14 questions: 7 about anxiety and 7 about depression. It is an assessment that measures mild to moderate depression in PPs *[Schrag 2007].*
3. Comparison between the structural and activation maps of brain networks in order to identify biomarkers of the management of brain activity. The modulation of brain activity will also be assessed by means of a map of correlation coefficients representing the strength of connectivity between the different brain networks and regions of interest, obtained from functional MRI sequences at rest, [after – before] care. The main MRI sequences performed will be resting state acquisitions (resting functional imaging) and anatomical imaging (i.e. T1 imaging).
4.
[figure not shown]
Comparison between the 2 groups of patients of their analgesic response according to their personality profile.

**5. RESEARCH DESIGN**

## RESEARCH OUTLINE

Due to the lack of published data on the subject, it was chosen to conduct a pilot study, since FR has not yet been evaluated in a population of Parkinson's patients in order to reduce their chronic pain.

It is therefore a single-center, longitudinal, prospective, double-blind, randomized exploratory study in 2 parallel groups (1:1 ratio): 1 group benefiting from FR sessions, 1 control group benefiting from foot MS sessions. Both the patient and the pain assessor will be blinded.

## METHODS FOR RANDOMIZATION

Patients will be randomized into two groups in a 1:1 ratio, the experimental group that will receive the FR sessions and the control group that will receive the foot SM.

Randomization will be established by the MeDatas cell of the Clinical Investigation Center (CIC). When a subject is included, the assignment of a number and group will be established by means of a secure randomization interface via the CIC website.

Subjects will be randomized once the investigator verifies that they meet the eligibility criteria (Section 5). Patients will be randomized to one of 2 groups according to the chronological order of inclusion of patients in the protocol.

Randomization will be done at the inclusion visit. Only the person in charge of foot reflexology and sham massages ([name]) will be informed of the patient's randomization.

**6. ELIGIBILITY CRITERIA**

## INCLUSION CRITERIA

- Men and women ≥ 18 years old.
- Patients with no disabling dyskinesias judged by the investigator.
- Patients with chronic pain of any origin, regardless of the pathophysiological mechanism, for at least 3 months with VAS ≥ 4.
- Patients whose anti-Parkinson's treatment has been stable throughout the duration of the study and at least for 4 weeks.
- Person affiliated to or beneficiary of a social security scheme.
- Free, informed, written, and signed consent by the participant and the investigator (no later than the day of

, inclusion and prior to any review required by the research).

## CRITERIA FOR NON-INCLUSION

- Patients with cognitive impairment defined by a MOCA < 25.
- Patient included in a clinical trial that potentially interferes with the purpose of the study (interventional study, early study for a drug). - Patient refractory to foot massage.
- Patient who has benefited from a FR session in the last 6 months.
- Contraindication to foot reflexology: ATCD phlebitis less than 3 months; skin lesions on the feet or unresolved fractures on the feet.
- Patients with a contraindication to MRI: claustrophobic patient, patient with a metallic element.
- Patient refusing to be informed of any abnormality detected on brain MRI.
- Protected patient: adults under guardianship, curatorship or other legal protection, deprived of liberty by judicial or administrative decision.

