| **CRITERIA**  **INCLUSION** | - Men and women ≥ 18 years old. - Parkinson's disease with little fluctuation, i.e. with MDS UPDRS IV ≤ 2. - Patients who have chronic pain of any origin, regardless of the pathophysiological mechanism for at least 3 months with VAS ≥ 4. - Patients whose anti-Parkinson's treatment has been stable throughout the duration of the study and at least for 4 weeks. - Ability to provide informed consent. - Affiliation to a social security scheme or equivalent. |
| **CRITERIA FOR NON-INCLUSION** | - Patients with cognitive impairment defined by a MOCA < 25. - Patient included in a clinical trial that potentially interferes with the purpose of the study (interventional study, early study for a drug). - Patient refractory to foot massage. - Patient who has benefited from a PR session in the last 6 months. - Contraindication to foot reflexology: history of phlebitis less than 3 months old; skin lesions on the feet or unresolved fractures on the feet. - Patients with a contraindication to MRI: claustrophobic patient, patient with a metallic element. - Patient refusing to be informed of any abnormality detected on brain MRI. - Protected patient: adults under guardianship, curatorship or other legal protection, deprived of liberty by judicial or administrative decision. |
| **TREATMENTS/**  **RESEARCH STRATEGIES/ PROCEDURES** | Patients in the **experimental group** will receive 4 FR sessions, of one hour, spaced 3 weeks apart each. The FR will be carried out by [name], CNRS researcher, seconded to INSERM, trained and certified in reflexology. The specific PR protocol used in the present study was designed and standardized in collaboration with experienced reflexology practitioners. (It will be the same for all patients and for all sessions). This protocol stimulates the reflex zones associated with the management of pain, stress and emotions, it is described in part 7 "Treatment/Research strategies and procedures".    **Patients in the control group** will receive 4 sessions of SM, feet and calves, (without stimulating the foot reflexology points) of one hour, spaced 3 weeks apart by the same practitioner. This massage has been standardized and will be the same for all patients in this group and for all sessions. |
| **STUDY SIZE** | We will include 30 patients in this study divided into 2 groups of 15 patients. |

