**Eligibility criteria**

[figure not shown]
 Inclusion criteria: Adult ≥ 18, Little fluctuating Parkinson's disease attested by a score ≤ 2 on the MDS UPDRS IV, Patients with chronic pain for at least 3 months with a VAS ≥ 4 and Patients whose antiparkinsonian treatment is stable throughout the duration of the study and at least for 4 weeks.

[figure not shown]
 Exclusion criteria: Patients with cognitive impairment defined by an MOCA <25. Contraindication to carrying out the MRI examination (Pregnant or lactating woman, claustrophobic patient, patient carrying a metallic element), Patient refusing to be informed of any abnormality detected on brain MRI, Patient included in a clinical trial that potentially interferes with the objective of the study, Patient resistant to foot massage, Patient having benefited from a FR session in the last 6 months, skin lesions in the feet, recent fracture in the feet, history of phlebitis less than 3 months and history of deep vein thrombosis.

Arm number or label and arm type

Sham massage (SM) comparator will be a placebo massage of FR.

Two arm will be received the FR and SM.

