**Interventions**

The experimental group will receive 4 one-hour FR sessions spaced 3 weeks apart. FR will be performed by a researcher trained and certified in reflexology. The specific FR protocol used in this study was designed in collaboration with experienced reflexology practitioners and will be the same for all patients and for all sessions. This protocol stimulates the reflex zones associated with the management of pain, stress and emotions.

The control group will receive 4 sessions of SM, feet and calves, one hour, spaced 3 weeks apart, performed by the same researcher. This massage will be the same for all patients in this group and for all sessions. The estimated duration of the inclusion period is estimated to two years. The duration of each participant's participation is established to 12 weeks. The total duration of the research is established to three years.

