## TREATMENT/STRATEGY/COMPARISON PROCEDURE

The control group will receive 4 sessions of SM, feet and calves, of one hour, spaced 3 weeks apart by the same worker. Patients drawn at random from the group that will benefit from the SM will have a foot and calf massage without stimulating the foot reflexology points. This massage will be the same for all patients in this group and for all sessions.

The SM technique is exclusively manual, it is practiced with the hands. The pressure of the hands is perpendicular to the surface of the skin, for a few mm, and move according to the established protocol:

- Full Straightening (Foot + Calf) x3
- Malleoli Smoothing x3
- Full Calf Smoothing x3
- Inner kneading of the calf
- External kneading with the palm
- Friction
- Calf straightening x3
- Soft knee straightening
- Knee side smoothing x3
- Full Smoothing
- Heel straightening
- Pumping the hollow of the foot
- Arch pressure
- Foot smoothing
- Stress of the metatarsals
- Rotation and light toe stretching
- Foot Smoothing x3
- Smoothing between metatarsals
- Ankle Smoothing x3
- Soft-Sided Cat Paste

The content of the sessions, PR and MS, has been standardized, in order to guarantee the reproducibility of the study and its transfer to clinical practice.

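### The non-inclusion criteria protect only the feet, although the sham massage also works on calves and knees, and the three eligibility lists disagree on deep vein thrombosis

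*Protocol*

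**What the plan says.** **Non-inclusion item.** Section 6 (Criteria for non-inclusion) reads "Contraindication to foot reflexology: ATCD phlebitis less than 3 months; skin lesions on the feet or unresolved fractures on the feet". The research summary in section 1 has the same content: "Contraindication to foot reflexology: history of phlebitis less than 3 months old; skin lesions on the feet or unresolved fractures on the feet". The abstract (Eligibility criteria) also names only the feet for lesions and fractures, but ends its list with "history of phlebitis less than 3 months and history of deep vein thrombosis".

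**Control procedure.** The research summary says that control patients "will receive 4 sessions of SM, feet and calves, (without stimulating the foot reflexology points) of one hour". The abstract agrees: "The control group will receive 4 sessions of SM, feet and calves". The step list in section 7 (Treatment/strategy/comparison procedure) includes "Inner kneading of the calf" and "Knee side smoothing x3", along with kneading by the palm, friction and several smoothing strokes along the calf. The same section says that the massage does not vary between control patients or sessions.

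**Timing.** Section 5 (Methods for randomization) states: "Subjects will be randomized once the investigator verifies that they meet the eligibility criteria". Section 9 (Inclusion visit / randomization process) places the baseline evaluation after randomisation.

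**The concern.** Eligibility is decided before the arm is known, so one list has to suit both interventions. This list is drafted for one of them. By excluding foot lesions and foot fractures, the protocol accepts that damage where the practitioner's hands work is a reason not to include a patient. It applies that reasoning to the area treated by reflexology and not to the additional area treated by the sham.

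The thrombosis criterion is a different kind of problem. Three lists in the same version of the protocol answer one eligibility question in two ways, so whether a patient is admitted depends on which page the investigator reads.

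What is at stake is the safety of control patients and consistent application of the criteria. The comparison of pain scores is not affected.

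**Working it through.** No formula applies to the main point, so the check is a comparison of texts followed by a simple count.

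**The three eligibility lists**

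| List | Lesions and fractures limited to | Recent phlebitis (under 3 months) | Deep vein thrombosis |
| --- | --- | --- | --- |
| Section 6, Criteria for non-inclusion | feet | excluded, no site limit | not listed |
| Section 1, Research summary | feet | excluded, no site limit | not listed |
| Abstract, Eligibility criteria | feet | excluded, no site limit | any history excluded, no time limit |

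All 3 lists stop at the feet for lesions and fractures; 1 of 3 carries the thrombosis criterion.

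**Area treated in each arm**

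- Reflexology (section 7): the described technique is finger pressure on zones of the foot. The lists match this area.
- Sham (section 7): foot, calf and knee. The lists cover the foot only.

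**Two test patients**

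1. *A skin lesion on the calf, no other exclusion.* The patient is eligible under all three lists. If allocated to sham, the calf is kneaded at each of 4 sessions, and section 7 contains no instruction to leave an area out.
2. *A deep vein thrombosis more than 3 months ago.* The abstract excludes the patient; section 6 and the research summary admit the patient. Reading phlebitis broadly, so that it includes deep vein thrombosis, does not remove the conflict, because the 3-month limit in section 6 would still let this patient in.

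A recent phlebitis of the calf is already excluded, since that part of the item names no site. It is not part of this point.

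**Whether a later step closes the gap before allocation**

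- Sections 6 (Feasibility and recruitment procedures) and 9 (Pre-inclusion) provide for a physician to check eligibility, but against the listed criteria. A gap in the list carries through.
- The evaluation at the inclusion visit comes after randomisation. It contains questionnaires, a motor examination, the heat tests and MRI, with no listed check of leg skin or veins. The motor examination might well reveal an unhealed leg fracture, but that is an assumption.
- The item on patients refractory to foot massage concerns the foot and names no lesion, fracture or thrombosis.

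**Count of exposure**

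- Sham patients: 30 / 2 = 15.
- Sham sessions: 15 × 4 = 60, each including the calves.
- Chance that an admitted patient is allocated to sham: 15 / 30 = 1/2.

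The 60 sessions are simply all the planned sham sessions. They show where the mismatch applies and are not an estimate of harm.

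**The case against.** The strongest reply is that the protocol states no general rule against massaging near a lesion. It states one for reflexology, which uses focused finger pressure. The sham is a different technique, done with the whole hand and partly by smoothing, so extending the rule to it is an inference and a clinical one. This stands in part: the documents do not settle whether a given calf lesion, or an old thrombosis, rules out this massage. But the sham also includes kneading and friction of the calf, and the protocol gives no separate contraindications for it.

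A second reply is that physicians see the patient before allocation, that the practitioner talks to the patient before each session, that adverse events are collected, and that participation can be stopped for one. These safeguards are real. The physicians, however, apply the list as written. The other steps come after allocation, and section 9 does not replace patients who leave.

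Third, the thrombosis disagreement is narrow. It concerns only events more than 3 months old, and the abstract is the one list that differs. The documents do not show which version is intended, so the section 6 version cannot be called the wrong one. That is correct, and the recommendation is therefore only that the lists agree.

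Finally, the number of patients affected is unknown and may be zero. This stands, and it is why the point is minor.

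**Conclusion.** Both parts hold on the text of the current version. The lesion and fracture item does not cover the area massaged in the sham arm, and the abstract contradicts section 6 and the research summary on deep vein thrombosis. Followed as written, section 6 lets a patient with a calf lesion or an older thrombosis be randomised to calf massage.

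The severity is minor. The mismatch in area concerns the 15 planned sham patients; the thrombosis disagreement concerns the eligibility of any candidate. Neither changes the primary outcome, the sample size or any planned test. The conclusion about area assumes that the protocol's reason for excluding foot lesions and fractures is that the hands work there; whether the same caution is needed for each sham stroke is for the investigators to judge. The conclusion about thrombosis rests on the wording alone.

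**What to change.** 1. Reword the item in section 6 along these lines: *Contraindication to either intervention (reflexology or sham massage): phlebitis less than 3 months old; skin lesions or unresolved fractures of the feet, ankles, calves or knees.*
2. Decide on deep vein thrombosis. Either add it to section 6 and the research summary, or delete it from the abstract if the investigators judge it unnecessary.
3. Use the same text in all three lists. The abstract speaks of recent fractures and the other two of unresolved ones, which can be aligned at the same time.

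The cost is one eligibility line in three places, submitted through the amendment procedure in section 15 if recruitment has started. Some patients will become ineligible. The documents give no prevalence of leg lesions, leg fractures or older thrombosis, so the loss cannot be calculated. Section 6 cites 1500 patients followed, two thirds of them with pain, which is 1500 × 2/3 = 1000 before the other criteria are applied. Against 30 places, a loss large enough to threaten recruitment looks unlikely. If the investigators think that excluding every skin lesion up to the knee is too broad, they can restrict it to lesions that in their judgement preclude massage.
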